### Data analyses

Generalized Estimation Equation analyses (GEE) [41] will be used to test the efficacy of the intervention on the different outcome measures. Based on the scale level of the measurement and its distribution, logistic GEE-models, linear GEE-models or GEE-models for count variables will be applied. Potential baseline differences will be considered by adding additional baseline variables as covariates to the GEE-models. Both (1) complete case analyses (CCA) considering all study participants with available follow-up data and (2) intention to treat (ITT) analyses will be conducted. For the ITT analyses, the multiple imputations procedure (MICE) of STATA will be applied. Given the clustered nature of the data, robust variance estimators for all GEE-models will be computed, using the cluster option of STATA.

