### Sample size calculation

An estimation of the expectable effect size was based on the results of the pre-post study testing the initial efficacy of the program [22]. This study revealed a decrease in the percentage of persons with at least one RSOD occasion in the last month from 76% at baseline assessment to 68% at follow-up assessment. It is assumed that the improvements in the content and tailoring of the intervention will also result in an improved efficacy. Based on these considerations, it is assumed that the percentage of persons with at least one RSOD occasion in the last month at follow-up will be 76% in the control group and 66% or lower in the intervention group. A sample size of n = 322 in each study group would be required to have 80% power for a χ^2^-test (α = 5%, 2-sided) in order to detect this difference based on a calculation using *G-Power*
[25]. As students are nested within school classes, a potential design effect needed to be considered. Based on [22] an average cluster size of 10 study participants per school class and an intra-cluster correlation coefficient of 0.05 could be expected. This would result in a design effect of 1.45. Multiplying this design effect by the required size for an unnested sample (n = 322) results in a required sample size of n = 467 per study group and a total of n = 934 study participants.

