### Assessments and outcomes

At baseline, demographic variables (age, gender, educational level, and migration background) as well as characteristics of the schools and school classes will be assessed.

Baseline- and follow-up assessments will include:Frequency of RSOD occasions in the last 30 days (“How often did you have 5 (male; female: 4) or more drinks on one occasion in the last 30 days?”).Quantity of alcohol consumption, assessed by a 7-day drinking calendar similar to the Daily Drinking Questionnaire (DDQ) [37], for which participants were asked to think about a typical week in the past month and, for each day, to record the number of standard drinks they typically consumed on that day.Peak blood alcohol concentration assessed by asking participants to report the number of standard drinks consumed and the duration of their heaviest drinking episode in the previous 30 days. This information will be used along with the sex and weight to calculate an estimated peak blood alcohol concentration based on the Widmark Formula [38].Normative misperceptions of alcohol consumption using reference data from [39] and items derived from [14], who used modified versions of the first and second AUDIT-C [14, 40] items: “How often does a typical (male/female) secondary school student have a drink containing alcohol?” and “How many drinks does a typical (male/female) secondary school student have on a typical day when drinking alcohol?”.

The primary outcome of the planned study is RSOD in the past 30 days preceding the follow-up assessment. Secondary outcomes are (1) frequency of RSOD occasions in the past 30 days preceding the follow-up assessment, (2) peak blood alcohol concentration in the previous 30 days, (3) number of standard drinks consumed in a typical week of the preceding month, and (4) normative misperceptions of alcohol consumption in an age- and gender-specific reference group.

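### Covariates are tied to baseline differences rather than fixed in advance: committing to adjust for baseline RSOD would be a free improvement

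*Protocol article*

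**What the plan says.** The section Data analyses has one sentence on covariates: "Potential baseline differences will be considered by adding additional baseline variables as covariates to the GEE-models". It names no variable and does not say what counts as a difference. The same section says that "logistic GEE-models, linear GEE-models or GEE-models for count variables will be applied", according to the outcome's scale, and that "robust variance estimators for all GEE-models will be computed, using the cluster option of STATA".

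Under Assessments and outcomes, "The primary outcome of the planned study is RSOD in the past 30 days preceding the follow-up assessment". The item "Frequency of RSOD occasions in the last 30 days" is asked at both time points. RSOD frequency is a separate secondary outcome, and the sample size section works with the percentage of students with at least one occasion. The primary outcome is therefore binary and its model logistic.

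The sample size calculation assumes that this percentage "will be 76% in the control group and 66% or lower in the intervention group" and uses a chi-squared test without covariates. Classes are randomised within schools in blocks of 4; baseline drinking is not a stratification factor.

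**The concern.** Allocation is withheld from students until baseline data are in, and the staff supervising the baseline assessment are blinded. Baseline differences between arms should therefore be chance. A chance difference is a poor reason to choose a covariate; how well the variable predicts the outcome is a good one. The obvious predictor of RSOD at 6 months is RSOD at baseline, which is collected from everyone.

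Three things are at stake:

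- **Precision.** If baseline RSOD enters only when the arms happen to differ on it, the gain from adjustment is usually not taken.
- **The quantity estimated.** In a logistic model, adding a prognostic covariate changes the odds ratio being estimated, even with perfect balance. A covariate set settled after the comparison makes the target depend on the data.
- **Choice of model.** The baseline data include demographics, school and class characteristics and several drinking measures. With no set and no criterion stated, many adjusted models are possible.

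**Working it through.** **Inputs from the protocol article:** follow-up rates 76% and 66%; two-sided alpha 5%; power 80%; 322 per group before clustering; cluster size 10; intra-cluster correlation 0.05; 467 per group, 934 in total; baseline RSOD rate 76% (from the pre-post study). **Assumed, because the documents give no figure:** the correlation r between baseline and follow-up RSOD, and a p<0.05 trigger for adjustment.

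**1. The plan's own figure.** With mean rate 0.71,

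n = [1.96·√(2·0.71·0.29) + 0.8416·√(0.76·0.24 + 0.66·0.34)]² / 0.10² = (1.2578 + 0.5368)² / 0.01 = 322.0,

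which agrees with the stated 322 (323 if rounded up). The design effect is 1 + 9·0.05 = 1.45, and 322·1.45 = 466.9, giving 467 per group and 934 in total. The plan reproduces, and its 80% takes no credit for baseline adjustment.

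**2. Gain from fixed adjustment.** Adjustment multiplies the residual variance by about (1 − r²), so the effective unclustered n is 322/(1 − r²). Power = Φ{[0.10·√n − 1.2578] / 0.6378}.

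| r (assumed) | Effective n per group | Power at N = 934 | Total N for 80% |
|---|---|---|---|
| 0 | 322 | 80% | 934 |
| 0.2 | 335 | 82% | 898 |
| 0.3 | 354 | 84% | 850 |
| 0.4 | 383 | 86% | 786 |
| 0.5 | 429 | 90% | 702 |

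**3. What an imbalance-triggered rule keeps.** A simulation used 94 classes of 10, a binary intra-cluster correlation of about 0.05, logistic models with working independence and cluster-robust standard errors, and 3,000 runs per scenario. Here r is the correlation of the two binary measures.

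| r | Power, never adjusted | Power, adjusted only if baseline RSOD differs at p<0.05 | Power, always adjusted | Type I error of the triggered rule |
|---|---|---|---|---|
| 0.24 | 79.0% | 79.4% | 83.2% | 4.9% |
| 0.38 | 80.1% | 81.4% | 88.0% | 4.4% |
| 0.57 | 80.0% | 82.3% | 95.5% | 4.1% |

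The trigger fired in only 5% to 6% of the trials simulated with an effect. The rule kept 0.4 of 4.1, 1.3 of 7.9 and 2.2 of 15.5 points of the gain. The simulated gains are somewhat larger than the formula's, plausibly because class effects were also assumed to persist over time.

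**4. Size of a chance imbalance.** The standard error of the baseline RSOD difference is √(2·0.76·0.24·1.45/467) = 0.0337, or 3.4 points. A difference of up to 1.96·3.37 = 6.6 points would not trigger adjustment at p<0.05. Given an imbalance d, the unadjusted estimate shifts by about r·d. At r = 0.4 that is 1.3 points for a one-standard-error imbalance and 2.6 points at the threshold, against a 10-point target.

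**5. The odds ratio changes with the model.** The planned rates give an unadjusted odds ratio of (0.66/0.34)/(0.76/0.24) = 0.61. Take 76% RSOD at baseline and r = 0.4. Control follow-up rates are then 0.76 + 0.4·0.24 = 0.856 in students with baseline RSOD and 0.76 − 0.4·0.76 = 0.456 in the others. The common conditional odds ratio that brings the overall rate down to 66% is about 0.56: it turns 0.856 into 0.769 and 0.456 into 0.319, and 0.76·0.769 + 0.24·0.319 = 0.661. The same 10-point effect thus reads as 0.61 or 0.56, depending on whether baseline RSOD is in the model.

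**The case against.** The sentence does not say that covariates enter only in response to observed differences. It speaks of potential differences, and it prescribes no baseline test or p-value. The word additional could mean additional to a baseline term already in the model. This is also a journal article, and naming the covariate set is commonly left to an analysis plan, which is not shown here. All of this stands, and it limits the point to the reason the article itself gives for adjusting. That reason is baseline differences, and no baseline term is stated to which others could be additional.

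A reader might also infer that the primary result will be biased. The documents do not support that. Over the randomisation the unadjusted comparison is unbiased, and the shifts in step 4 are part of the sampling variation that the 80% power and 5% alpha already allow for. The 2.6 points is an edge case, and 3.4 points may be too high because it ignores stratification by school. The simulated trigger on a single covariate did not inflate type I error. Selection among many adjusted models could do harm, but that was not simulated and no figure is attached to it.

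Finally, the gain rests on an assumed correlation. At r = 0.2 it is only about 2 points of power.

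**Conclusion.** The point holds as a free improvement, not as an error that must be corrected before the trial can be trusted. The article makes baseline differences the reason for adjusting and does not commit to baseline RSOD. Its natural reading leaves the covariate set and the conditional odds ratio open after the arms are compared.

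Fixed adjustment is worth about 2 to 10 points of power at N = 934 for correlations of 0.2 to 0.5. A p<0.05 trigger would keep roughly a tenth to a sixth of the simulated gain. The correlation and the trigger are assumptions.

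It would be wrong to conclude that the trial is underpowered. The sample size reproduces on an unadjusted test, so the loss is precision forgone, not a shortfall below 80%.

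**What to change.** Replace the covariate sentence in Data analyses with: 'Each model will adjust for the baseline value of its outcome (for the primary outcome, baseline RSOD), whatever the observed balance; any covariates added because of baseline differences will be used in sensitivity analyses only.' Add: 'For the primary outcome, a standardised (marginal) risk difference will be reported beside the odds ratio.'

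All outcome measures are already taken at both time points, so no new data are needed and the sample size can stay as it is. The cost is two sentences and one post-estimation step, settled before the arms are compared. If an analysis plan already fixes baseline RSOD as a covariate, it is enough to bring the article's sentence into line with it. Whether other variables deserve a fixed place is for that plan to decide on prognostic grounds.

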## Discussion

This study protocol presents the design of a cluster randomised controlled trial testing the efficacy of a combined web- and text messaging-based intervention to reduce problem drinking in young people. Although web-based interventions have been applied and tested for nearly all modifiable and preventable risk factors [42–44], the efficacy of mobile phone text messaging or combined web- and text messaging-based interventions has not received much scientific attention so far. This is the first study testing the efficacy of a combined web- and text messaging-based intervention to reduce problem drinking in young people and one of the few studies testing the efficacy of a web-based intervention to reduce problem drinking in young people with heterogeneous educational level. In contrast to individual face-to-face counselling, counselling via Internet and text messaging is more economic and matches with the lifestyle and communication habits of young people. Given that this intervention approach proves to be effective, it could be disseminated to various groups of adolescents and young adults, e.g. in schools or at workplaces.

## Abbreviations

RSOD: Risky single-occasion drinking.
